# Live birth after fresh versus frozen single blastocyst transfer (Frefro-blastocyst): study protocol for a randomized controlled trial

**DOI:** 10.1186/s13063-017-1993-5

**Published:** 2017-06-05

**Keywords:** Single embryo transfer, Blastocyst, Singleton live birth, Randomized controlled trial

## Abstract

**Background:**

Multiple pregnancies are one of the major safety concerns of in vitro fertilization (IVF) due to the increased risk of maternal and neonatal complications. Single embryo transfer is the most effective way to reduce the risk of multiple pregnancies. Selection of the embryo and optimization of the implantation environment are crucial to retain the success rate when the number of transferred embryos is diminished. Fresh embryo transfer with supra-physiological levels of hormones has been suggested to have an adverse effect on implantation. Elective frozen embryo transfer has been suggested to result in a higher rate of live birth than fresh embryo transfer. However, there is still a lack of evidence from randomized clinical trials comparing the efficacy and safety between frozen and fresh single blastocyst transfers.

**Methods/design:**

We are conducting a randomized controlled trial in women aged 20–35 undergoing their first cycle of IVF with or without intracytoplasmic sperm injection. After ovarian stimulation with a gonadotropin-releasing hormone antagonist protocol, women who obtain four or more embryos on day 3 of the embryo culture are randomized into two parallel groups: a single fresh blastocyst transfer group and a single frozen blastocyst transfer group (all blastocysts vitrified and a deferred frozen blastocyst transfer). The primary outcome is singleton live birth.

**Discussion:**

The results of this study will provide evidence for the efficacy and safety of the strategy of elective frozen single blastocyst transfer in women with a good prognosis.

**Trial registration:**

Chinese Clinical Trial Registry, ChiCTR-IOR-14005405. Registered on 30 Oct 2014.

**Electronic supplementary material:**

The online version of this article (doi:10.1186/s13063-017-1993-5) contains supplementary material, which is available to authorized users.

## Background

Since the birth of the first baby conceived by in vitro fertilization (IVF) in 1978, IVF has been increasingly used worldwide [1]. Historically, to compensate for the low rate of implantation of individual embryos and achieve acceptable pregnancy rates, multiple embryos were transferred at a time. As the implantation rate continues to improve with the advancements in embryo culture, concerns have increasingly been raised on the risk of multiple pregnancies. The number of embryos transferred has been reconsidered [2, 3]. By reducing the number of embryos transferred to two, the incidence of high-order pregnancies has been dramatically decreased without compromising the pregnancy rate [4]; however, the risk of twin pregnancies remains unchanged [5]. Elective single embryo transfer (eSET) is the most effective approach to reduce the risk of twin pregnancies [3, 6]. eSET is recommended to patients with a good prognosis: age <35 years, more than one top-quality embryo available for transfer, first or second treatment cycle [5]. However, the adoption of the eSET policy has been slow because of concerns about the decreased pregnancy rate after single embryo transfer compared with double embryo transfer [2, 3, 7]. Selection of the embryo and optimization of the uterine environment are crucial to retain the success rate.

In order to improve the selection of the embryo, extended culture to the blastocyst stage has been increasingly utilized. Blastocysts are suggested to have greater implantation potential than cleavage-stage embryos [8]. Single blastocyst transfer has resulted in significantly higher rates of pregnancy and delivery than single cleavage-stage embryo transfer [9]. To optimize the uterine environment, frozen embryo transfer may be a better choice than fresh embryo transfer. Controlled ovarian hyperstimulation and the resulting supra-physiological hormones have been suggested to have a detrimental effect on oogenesis, implantation of embryos [10], endometrial development [11] and frequency of uterine contraction [12], and perhaps perinatal outcomes [13]. Frozen embryo transfer allowing the recovery of supra-physiological hormones and the shedding of the exposed endometrium may provide a better physiological environment for embryo implantation. On the other hand, developments in the technology of cryopreservation, especially the introduction of vitrification, has greatly increased the survival rate of the embryo after thawing and enabled a non-inferior pregnancy rate after frozen embryo transfer compared with fresh embryo transfer [14]. Recently, a freeze-all and delayed frozen embryo transfer policy has been advocated and has achieved wide popularity [15–17]. In patients with polycystic ovary syndrome (PCOS), by transferring cleavage-stage embryos, we had observed that frozen embryo transfer resulted in a higher rate of live birth, a lower rate of ovarian hyperstimulation syndrome (OHSS), and a higher birth weight of the singleton, but a higher risk of preeclampsia compared with fresh embryo transfer [18]. However, there is still a lack of evidence as to whether a frozen blastocyst transfer could also provide any advantage over a fresh blastocyst transfer. A randomized trial is warranted to test the efficacy and safety of the strategy of single frozen blastocyst transfer. This study is a multicenter randomized controlled trial comparing the efficacy and safety of single frozen blastocyst transfer with single fresh blastocyst transfer in women with a good prognosis.

## Methods/design

### Study population

#### Inclusion criteria

The inclusion criteria are as follows:Women aged ≧20 and <35 yearsWomen with regular menses (defined as a spontaneous cycle length of 21–35 days)Women who are undergoing their first cycle of IVF or intracytoplasmic sperm injection (ICSI)Women with ≧4 day-3 embryos suitable for transfer.

#### Exclusion criteria

The exclusion criteria are as follows:Women who have been diagnosed with congenital or acquired uterine abnormalities such as uterine malformation (uterus unicornis, septate uterus, or duplex uterus), adenomyosis, submucous myoma, or intrauterine adhesionWomen who are to undergo preimplantation genetic diagnosis/preimplantation genetic screeningWomen who are to undergo frozen embryo transfer before randomization such as those who are scheduled to be treated for hydrosalpinx, who have elevated progesterone during controlled ovarian hyperstimulation, or who have high risk of severe OHSSWomen with medical conditions that contraindicate assisted reproductive technology and/or pregnancy, such as uncontrolled hypertension or known symptomatic heart disease; poorly controlled type 1 or type 2 diabetes mellitus; undiagnosed liver disease or dysfunction (based on serum liver enzyme test results); renal disease or abnormal serum renal function; severe anemia; history of deep venous thrombosis, pulmonary embolus, or cerebrovascular accident; history of (or suspected) cervical carcinoma, endometrial carcinoma, or breast carcinoma.

### Study intervention

#### Screening

At the screening visit, written informed consent will be obtained from the couples. Previous medical history and current medication status are reviewed with the standardized case report forms. A physical examination and transvaginal ultrasound scan are performed. Laboratory measurements including basal sex hormone tests, safety assays such as liver function, renal function, hepatitis virus, HIV, syphilis, coagulation, blood routine, and urine routine are performed in the local labs of the study sites. All of the subjects and their partners are karyotyped to exclude couples with abnormal karyotype. A diagnostic hysteroscopy is performed in patients who are suspected to have an abnormal uterine cavity. A schedule of enrollment, interventions, and assessment is provided in the Standard Protocol Items: Recommendations for Interventional Trials (SPIRIT) figure (Fig. 1). The flow chart of this study is given in Fig. 2.

**Fig. 1 Fig1:**
[figure not shown]
SPIRIT figure: the schedule of enrollment, interventions, and assessments

**Fig. 2 Fig2:**
[figure not shown]
Flow chart of subjects

#### Controlled ovarian hyperstimulation

The gonadotropin-releasing hormone (GnRH) antagonist protocol is used for ovarian stimulation in all subjects. Recombinant follicle-stimulating hormone (rFSH, Puregon; MSD Organon, Oss, The Netherlands) is started on days 1–3 of the menstrual cycle. The dose of rFSH is adjusted according to ovarian response monitored by hormone tests and transvaginal ultrasound scan. Human menopausal gonadotropin can be added at the discretion of local investigators. GnRH antagonist ganirelix (MSD Organon, Oss, The Netherlands) at a daily dose of 250 μg is administered when there is at least one follicle ≥12 mm in mean diameter until the trigger day (including the trigger day). Human chorionic gonadotropin (hCG) at a dose of 4000–10,000 IU will be administered when at least two follicles are ≥18 mm in mean diameter.

#### Oocyte retrieval, in vitro fertilization, and embryo culture

Transvaginal ultrasound-guided follicle aspiration is performed 34–36 h after hCG injection by experienced physicians. Oocytes are inseminated by IVF or ICSI according to the quality of sperm. If the total number of motile sperm is below 5 million, ICSI is performed. Mixed IVF and ICSI as half ICSI (50% oocytes are inseminated by IVF and 50% oocytes by ICSI) or rescue ICSI (if the second polar body is absent in more than 60% of oocytes after IVF, these oocytes will be re-inseminated by ICSI) are also allowed.

On day 3 of the embryo culture, the quality of embryos is assessed by morphological criteria mainly based on the number and regularity of blastomeres as well as the percentage of fragmentation. Subjects with four or more embryos that are suitable for transfer are randomly assigned to the fresh or frozen blastocyst transfer group. Blastocyst culture is performed for all embryos of the randomized subjects.

#### Randomization

Block randomization is used to assign subjects to treatment groups with a 1:1 ratio. The randomization is stratified by study site. The sequence of randomization has been generated by biostatisticians in data coordinator center with SAS software version 9.2 (SAS Institute, Cary, NC, USA). The original sequence is safely kept by the staff in the data coordinator center, and it has been input into the online central randomization system by these staff members, who are not involved in enrolling subjects. The online sequence is not accessible to any investigators or study coordinators. If a subject fulfills the enrollment criteria, the authorized investigator or study coordinator will login the password-protected account to get the assignment for her. After randomization, both subjects and investigators are informed about the assignments.

#### Single fresh blastocyst transfer

On day 5 of embryo culture, women who are assigned to the fresh blastocyst transfer undergo a single blastocyst transfer. Luteal phase support with vaginal progesterone gel (Crinone, Merck Serono, Darmstadt, Germany) 90 mg/day and oral dydrogesterone 10 mg twice daily is started from the day of oocyte retrieval and continued until 12–15 days after embryo transfer when serum hCG is measured to determine pregnancy. If pregnancy is achieved, luteal phase support will be continued until 10 weeks’ gestation.

#### Single frozen blastocyst transfer

On day 5 of embryo culture, women who are assigned to the frozen blastocyst transfer group have their blastocysts vitrified. Luteal phase support that started from the day of oocyte retrieval with the same regimen as the fresh blastocyst transfer group will be stopped after randomization. At least 4 weeks later, endometrium preparation is performed with a natural cycle regimen or hormone replacement cycle regimen, at the discretion of local investigators.

For the natural cycle regimen, ovulation is determined by ultrasound monitoring. Local investigators decide whether to use hCG for ovulation triggering according to their clinical routine. Luteal phase support is started from the ovulation day with oral dydrogesterone 10 mg three times daily. A single frozen-thawed blastocyst will be transferred 5 days after ovulation. If the patient is pregnant, luteal phase support will continue until 10 weeks’ gestation.

For the hormone replacement cycle regimen, the endometrium is prepared with oral estradiol valerate at a dose of 4–8 mg daily started on day 1 to day 3 of the menstrual cycle. Vaginal progesterone gel (Crinone, Merck Serono) 90 mg/day and oral dydrogesterone 10 mg twice daily are added when the endometrial thickness reaches 7 mm or more. A single frozen-thawed blastocyst will be transferred 5 days after progesterone initiation. Estradiol valerate at the dose for endometrium preparation will be continued until the day of the hCG test. If pregnancy is achieved, estradiol valerate is stopped gradually at 8 to 9 weeks of gestation; vaginal progesterone gel and oral dydrogesterone is continued until 10 weeks of gestation.

#### Outcome and outcome assessments

The primary outcome is singleton live birth. The secondary outcomes include conception, clinical pregnancy, ongoing pregnancy, pregnancy loss, live birth, moderate and severe OHSS, ectopic pregnancy, pregnancy and perinatal complication, birth weight, neonatal complication, and other adverse events.

Regarding conception, serum β-hCG is measured to determine pregnancy 12 days after embryo transfer. Conception is defined with the result of serum β-hCG ≥10 mIU/mL.

Regarding clinical pregnancy, if a conception is achieved, a transvaginal ultrasound scan is performed 20 days later. Clinical pregnancy is defined as detection of a gestational sac in the uterine cavity. An ectopic pregnancy is defined as one in which the embryo implants at any site other than the endometrial lining of the uterine cavity.

For an ongoing pregnancy, a transvaginal ultrasound scan is repeated at 11–12 weeks’ gestation. Ongoing pregnancy is defined as detection of a viable fetus with fetal heartbeat.

During pregnancy, women are contacted by telephone call every 3 months to inquire about adverse events. Pregnancy loss is defined as pregnancies that eventuate in a spontaneous abortion or therapeutic abortion that occurred during the pregnancy.

At delivery, obstetrical and perinatal complications as well as neonatal information are obtained with reference to obstetric medical records and neonatal medical records. A singleton live birth is defined as the delivery of one newborn ≥28 weeks’ gestation with heartbeat and breath. A live birth is defined as the delivery of any number of newborns ≥28 weeks’ gestation with heartbeat and breath.

At 6 weeks after delivery, postpartum complications and neonatal complications are followed up by telephone call.

Moderate OHSS is diagnosed when ultrasonographic ascites is present in addition to abdominal distension and discomfort with or without nausea, vomiting, and/or diarrhea. Severe OHSS is diagnosed when there is clinical evidence of ascites and/or hydrothorax or breathing difficulties with or without hemoconcentration, coagulation abnormalities, and diminished renal function.

Adverse events are any untoward or unfavorablemedical occurrences associated with the subject’s participation in the research, whether or not considered related to the study intervention. Serious adverse events are events that are temporally associated with the subject’s participation in research that meet any of the following criteria: death, life-threatening, severely or permanently disabling, requiring in-patient hospitalization or prolongation of existing hospitalization, pregnancy loss after 20 weeks gestation, neonatal death up to 6 weeks after delivery, congenital anomaly or birth defect, or any events deemed as serious by the local principal investigator.

### Data analysis

#### Sample size calculation

Based on the retrospective data from our IVF clinic, the live birth rate following single fresh blastocyst transfer in patients younger than 35 years is about 50%. It was assumed that an absolute difference of 10% in live birth rate will be of clinical significance. We aim to test a difference of 10% of live birth rate between treatment groups (i.e., 50% in the fresh group and 60% in the frozen group) at a significance level of 0.01 with a statistical power of 90%. The minimal sample size calculated is 735 for each group. In consideration of a dropout rate of 10%, we will enroll 817 subjects in each group.

#### Data collection

Data are collected with a standard case report form developed in the web-based data entry system with real-time logical and range checking. Data are de-identified before being input into the database. Regular study site monitor and database checking are performed to ensure the accuracy of data collected.

#### Data analysis plan

The primary analysis will use an intent-to-treat approach to examine differences in the singleton live birth rate in the two treatment arms using the Pearson chi-square test. Safety parameters and secondary efficacy parameters, such as pregnancy rate, OHSS rate, and other rates, will be analyzed using the Pearson chi-square test. A secondary per-protocol analysis will be performed according to the actual treatment that subjects received. Continuous data were expressed as mean ± standard deviation with a Wilcoxon rank sum test for testing between-group differences. Categorical data were represented as frequency and percentage; differences in these measures between treatment groups were assessed by chi-square analysis, with Fisher’s exact test for expected frequencies less than 5.

The flow chart of this study is given in Fig. 2, and the SPIRIT checklist is included as Additional file 1.

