In women with a good prognosis, i.e., those who are defined as young and undergoing their first IVF cycle and obtaining four or more day-3 transferrable embryos in this study, eSET is recommended to reduce the risk of multiple pregnancies. However, the adoption of this policy has been slow due to concerns about the diminished pregnancy rate. Extending embryo culture to the blastocyst stage to improve embryo selection has been demonstrated as an effective measurement. Whether replacing the well-selected embryo into a more physiological uterine environment could further increase the chance of live birth of eSET is of great clinical significance. This study is expected to provide a reliable answer.

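### The primary chi-square test ignores study site, the only stratification factor, and two covariates known before allocation; prespecified adjustment would give a small efficiency gain at little cost

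*Protocol article*

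**What the plan says.** Under Outcome and outcome assessments: "The primary outcome is singleton live birth". The Data analysis plan says the primary analysis will "examine differences in the singleton live birth rate in the two treatment arms using the Pearson chi-square test", by intention to treat. It names no covariate or stratum for that comparison.

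The Randomization section describes 1:1 block allocation stratified by study site only. The Discussion expects more than 20 centers.

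Two other variables are fixed before allocation. Age is an inclusion criterion (20 to under 35 years). Embryo number is assessed on day 3, and only then is allocation made: "Subjects with four or more embryos that are suitable for transfer are randomly assigned". The Discussion describes women with a good prognosis as "those who are defined as young and undergoing their first IVF cycle and obtaining four or more day-3 transferrable embryos in this study".

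The Sample size calculation assumes "50% in the fresh group and 60% in the frozen group", tested "at a significance level of 0.01 with a statistical power of 90" per cent. It continues: "The minimal sample size calculated is 735 for each group". Then: "In consideration of a dropout rate of 10%, we will enroll 817 subjects in each group".

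**The concern.** Stratifying by site makes the arms nearly balanced within each center. If live birth rates differ between centers, this balance reduces the true variance of the difference between arms. The crude chi-square uses a variance that does not recognize the reduction, so it rejects somewhat less often than its nominal level, and the matching interval is a little too wide.

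Age and embryo count are a separate matter. They are not stratification factors, so leaving them out does not disturb the type I error. It does give up any precision they could supply. Embryo count has an entry floor of four and no stated upper limit, so it can still vary among the women enrolled. Randomization on day 3 precedes transfer or vitrification on day 5. It is therefore plausible, though the article does not say so, that the count affects whether a blastocyst is available at all. Age is confined to a narrow band and is probably the weaker of the two.

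At stake is a modest amount of precision at a strict significance level. All three variables should already be on record for every woman.

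**Working it through.** **Step 1. Reproduce the planned size.** Inputs from the Sample size calculation: 0.50 and 0.60, level 0.01, power 90%. The article does not state the sidedness; two-sided is used here because it reproduces the stated figure. With the pooled-variance formula for two proportions and no continuity correction:

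n = [2.576 × √(2 × 0.55 × 0.45) + 1.282 × √(0.50 × 0.50 + 0.60 × 0.40)]² / 0.10² = (1.812 + 0.897)² / 0.01 ≈ 734.05, rounded up to **735**.

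With 10% dropout: 735 / 0.90 = 816.7, rounded up to **817**. Both figures match. The one-sided version gives 643 and does not. Power of the unadjusted test is 90.0% with 735 per arm analysed, and 93.2% if all 817 are.

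**Step 2. Effect of adjustment.** Let R² be the share of outcome variance explained by the adjusting variables. The article gives nothing from which to derive it, so it is varied. Variance is multiplied by (1 − R²), the standard error by √(1 − R²), the required n becomes 735 × (1 − R²), and power at 735 is that of an unadjusted trial with 735 / (1 − R²) per arm.

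| Assumed R² | Reduction in standard error | n per arm for 90% power | Power at 735 per arm |
|---|---|---|---|
| 0% | 0% | 735 | 90.0% |
| 1% | 0.5% | 728 | 90.4% |
| 2% | 1.0% | 721 | 90.7% |
| 3% | 1.5% | 713 | 91.0% |
| 5% | 2.5% | 699 | 91.7% |

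**Step 3. What R² might be.** All associations here are assumptions.

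- Age SD and embryo-count SD of about 3 each, with odds ratios from 0.99 to 0.90 per year and from 1.02 to 1.10 per embryo: R² about 0.1% to 4%, power 90.1% to 91.4%.
- Odds ratio 1.2 per SD for each variable: R² about 1.6%, power 90.6%.
- The same plus a between-site SD of 0.3 on the log-odds scale: R² about 3.6%, power 91.2%. Site thus contributes about 3.6 − 1.6 = 2.0 percentage points.

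**Step 4. How conservative the crude test is.** If site explains 2% and allocation is balanced within site, the crude statistic has a true standard deviation of about √0.98 = 0.990 under no effect. The nominal cut-off of 2.576 then acts like 2.576 / 0.990 = 2.602, a two-sided error of about 0.0093 instead of 0.0100. For the site component, Step 2 slightly overstates the power gain, because stratified allocation has already given the crude difference some of the benefit.

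**Step 5. Whether adjustment can cost anything.** The full model was simulated with 22 sites, two covariates and 1,470 women (2 × 735). With nothing prognostic, the variance differed by only 0.3% and the type I error was 1.0%. With modest assumed effects, variance fell by about 2% and power rose by about 1 point.

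**Step 6. Chance imbalance.** The standard error of a between-arm covariate difference is √(2/735) ≈ 0.052 SD. At an odds ratio of 1.2 per SD, a one-standard-error imbalance moves the risk difference by about ln 1.2 × 0.55 × 0.45 × 0.052 ≈ 0.002, or 0.2 percentage points, against a 10-point target. This is a minor reason to adjust.

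**The case against.** The strongest reply is that nothing is wrong. The chi-square is valid under randomization, needs no model, addresses the absolute difference on which the trial was sized, and delivers the stated 90% power. Supportive adjusted analyses are commonly left to an analysis plan, which is not shown here. All of this stands, and it is why the point is one of efficiency only. It does not remove the point, because the article itself fixes which analysis is primary.

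A reader might infer that the protocol declares age and embryo count prognostic among the women enrolled. It does not. The Discussion uses them as entry thresholds for a good prognosis and gives no gradient within 20 to under 35 years or above four embryos. Restricting entry tends to shrink whatever gradient exists.

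A reader might also expect a gain of 2 points or more. That needs strong associations: odds ratios of 1.5 per SD for both variables give R² of about 7.1% and power of 92.4%. With an assumed age SD of 3 years, 1.5 per SD implies 1.5^(14/3) ≈ 6.6-fold odds between ages 20 and 34. Nothing in the article supports an effect of that size.

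Two practical objections have weight. Some of the more than 20 centers may be small, which can destabilize a model with one term per site; pooling small sites answers this. And more than 300 women were enrolled when the article was written, with assignments known to subjects and investigators, so changing the primary test needs a dated justification.

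**Conclusion.** The point holds as a modest improvement. The crude test omits the one stratification factor and two variables fixed before allocation. It is not invalid, and the trial is not underpowered because of it. For R² of 0 to 5%, variance falls by 0 to 5% and power at 735 per arm rises by about 0 to 1.5 points (1.7 at the very top of that range), equivalent to at most 735 − 699 = 36 women per arm. The gain may be nil: it rests wholly on assumed associations, since the article supplies none. The case for including site is the firmest, because it follows from the design; the case for embryo count and age rests on plausibility. What makes the change worthwhile is the lack of a statistical penalty: with nothing prognostic, the adjusted analysis lost essentially no precision and kept its error rate.

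**What to change.** Before outcome data are analysed, prespecify as primary a logistic model for singleton live birth, by intention to treat, with terms for treatment, study site, age (continuous) and day-3 transferable embryo count at randomization (continuous). State in advance the rule for pooling small sites. Report the standardized (marginal) risk difference with its confidence interval and test it at 0.01. This keeps the absolute difference in singleton live birth as the quantity estimated, so the sample size basis is unaffected. Retain the Pearson chi-square as a supportive analysis.

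No new data and no further women are needed. The costs are some programming, a slightly more complex primary analysis, and a dated, reasoned change to the plan while enrollment is under way, made without reference to outcomes by arm.

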## Discussion

This is a study comparing the efficacy and safety of single frozen blastocyst transfer with single fresh blastocyst transfer in women with a good prognosis. We plan to enroll 1618 subjects from more than 20 academic IVF centers in China. The enrollment began in August 2016. At the time of manuscript preparation, more than 300 subjects have been enrolled. The result of this large multicenter randomized trial will provide level I evidence for the strategy of single frozen blastocyst transfer in patients with a good prognosis.

Elective embryo cryopreservation followed by frozen embryo transfer, i.e., the freeze-all strategy, has attracted increasing attention and has been considered as a potential innovation of IVF treatment [15]. However, there are still great gaps in the literature to illuminate the risk/benefit ratio of this strategy, which includes multiple steps of treatment [19]. Four randomized trials compared frozen versus fresh embryo transfer [18, 20–22]. However, the stage and the number of embryos transferred varied among studies. Embryos were frozen by the slow-freezing method at 2PN stage in the earlier studies [20–22]. In a recent study in women with PCOS, embryos were vitrified at the cleavage stage, and two embryos were transferred [18]. There are several striking differences in uterine condition and embryo characteristics between cleavage-stage embryo transfer and blastocyst transfer. It was observed that uterine contractility had been significantly decreased at the time of fresh blastocyst transfer compared with that at the time of fresh cleavage-stage embryo transfer, and high-frequency uterine contraction was suggested to negatively impact the outcome of IVF via the dislocation of the embryo or disruption to the interaction between embryo and endometrium [23, 24]. Additionally, there were concerns regarding epigenetic modifications during blastocyst culture. A meta-analysis pooling six observational studies demonstrated that singleton pregnancies following blastocyst transfer were associated with higher risks of preterm birth and congenital anomalies compared with those following cleavage-stage embryo transfer [25]. Whether these differences necessarily translate to less superiority of frozen blastocyst transfer over fresh blastocyst transfer is unknown.

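### Randomization is stratified by study site but the primary test is an unstratified chi-square: valid and still at the planned power, but slightly conservative, and free to improve

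*Protocol article*

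**What the plan says.** The Randomization section of the protocol article states: "Block randomization is used to assign subjects to treatment groups with a 1:1 ratio." It adds: "The randomization is stratified by study site." The Discussion gives the scale as "more than 20 academic IVF centers in China".

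The Data analysis plan sets an intention-to-treat primary analysis of "differences in the singleton live birth rate in the two treatment arms using the Pearson chi-square test". It names the same test for the secondary efficacy and safety rates, with Fisher's exact test where expected counts are small. The article mentions no stratification or adjustment by site in any analysis.

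The Sample size calculation plans for "50% in the fresh group and 60% in the frozen group", "at a significance level of 0.01" and 90% power: "The minimal sample size calculated is 735 for each group." Allowing for 10% dropout raises this to 817 per group. The article gives no figure for how much live birth rates vary between centers.

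**The concern.** Blocked 1:1 allocation within each site keeps the arms nearly balanced on site. A center with a high or low live birth rate then contributes about equally to both arms, and its level cancels from the difference between them. The pooled Pearson test ignores this. It computes its standard error from the total variance p(1−p), which includes the variation between sites. When site rates differ, that standard error is larger than the true sampling variability of the difference.

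Some spread between sites is plausible on the article's own terms. Adding menopausal gonadotropin, the choice between natural-cycle and hormone-replacement preparation, and ovulation triggering in natural cycles are all left to local investigators. The 50% planning rate comes from a single clinic, so it gives no evidence of a common rate across centers.

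What is at stake is efficiency: a real type I error below the nominal 0.01, and somewhat less power than a stratified analysis of the same women would have.

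**Working it through.** **Inputs from the article.** Rates 50% and 60%, alpha 0.01, power 90%, 735 per group (817 after dropout), and 1:1 blocked allocation by site. Sidedness is not stated. Two-sided is inferred, because the one-sided formula gives 643 and not 735. The sample size section speaks of live birth; the same rates are used here for singleton live birth.

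**Input that has to be assumed.** The between-site standard deviation (SD) of the live birth rate, τ, taken as 0.05, 0.10 or 0.15.

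**1. The plan's own figure.** For the unstratified two-proportion test with pooled null variance:

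n = [2.576 × √(2 × 0.55 × 0.45) + 1.282 × √(0.50 × 0.50 + 0.60 × 0.40)]² / 0.10² = 734.05, rounded up to 735.

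735 / 0.90 = 816.7, rounded up to 817. Both figures reproduce, so the sample size was computed for the crude test that the plan names.

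**2. Variance that the crude test overcharges.** The total variance at the mean rate is 0.55 × 0.45 = 0.2475. The within-site variance is 0.2475 − τ².

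| τ | Within-site variance | Ratio to 0.2475 | Ratio of standard errors |
|---|---|---|---|
| 0.05 | 0.2450 | 0.990 | 0.995 |
| 0.10 | 0.2375 | 0.960 | 0.980 |
| 0.15 | 0.2250 | 0.909 | 0.953 |

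**3. True type I error of the crude test.** Alpha = 2 × [1 − Φ(2.576 / ratio of standard errors)].

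- τ = 0.05: 2.576 / 0.995 = 2.589, alpha 0.0096
- τ = 0.10: 2.576 / 0.980 = 2.629, alpha 0.0086
- τ = 0.15: 2.576 / 0.953 = 2.702, alpha 0.0069

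**4. Power for a 10-point difference.** Crude test: Φ[(0.10 − 2.576 × √(2 × 0.2475/n)) / √((0.49 − 2τ²)/n)]. Stratified test: the same, with 0.2475 − τ² in place of 0.2475 in the critical value.

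At n = 735 and τ = 0.10, the crude test gives (0.10 − 2.576 × 0.02595) / 0.02529 = 1.311, power 90.5%. The stratified test gives (0.10 − 2.576 × 0.02542) / 0.02529 = 1.365, power 91.4%.

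| τ | Crude, 735 | Stratified, 735 | Forgone (points) | Crude, 817 | Stratified, 817 | Forgone (points) |
|---|---|---|---|---|---|---|
| 0 | 90.0% | 90.0% | 0 | 93.2% | 93.2% | 0 |
| 0.05 | 90.2% | 90.4% | 0.2 | 93.3% | 93.5% | 0.2 |
| 0.10 | 90.5% | 91.4% | 0.9 | 93.7% | 94.3% | 0.6 |
| 0.15 | 91.1% | 93.0% | 1.9 | 94.2% | 95.5% | 1.3 |

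**5. Simulation check.** The setting was 21 equal sites with 35 women per arm per site (735 per arm), and an uncorrected Cochran-Mantel-Haenszel (CMH) test against Pearson. There were 200,000 runs for type I error and 40,000 for power.

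| τ | Type I error, Pearson | Type I error, CMH | Power, Pearson | Power, CMH |
|---|---|---|---|---|
| 0.05 | 0.0093 | 0.0096 | 90.0% | 90.4% |
| 0.10 | 0.0083 | 0.0099 | 90.3% | 91.2% |
| 0.15 | 0.0070 | 0.0101 | 91.2% | 92.9% |

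The simulation agrees with the formulas in direction and closely in size.

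**The case against.** The strongest reply is that nothing the plan promises fails. Sample size and primary test match each other, type I error stays at or below 0.01, and power for the stated difference stays at about 90% or better. The gain from stratifying depends on a spread that the article does not give. Narrow entry criteria (under 35, regular menses, first cycle, at least four usable day-3 embryos) and academic centers may keep that spread small. All of this stands, and it is why the point ranks low.

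Three stronger readings are tempting, and the document does not support them.

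- **The trial is underpowered or biased.** It is neither; the error is on the conservative side. A simulation can seem to show the Pearson test missing 90%. With a common odds ratio of 1.5 and sites spread by about 14 points, its power is 0.890. But the average difference in that setting is only about 9.3 points. The shortfall comes from the smaller effect, not from ignoring site.
- **The confidence intervals are too wide.** The article describes no interval for the primary comparison. What is too large is the standard error implied by the test.
- **No effect estimate is planned.** An article may leave effect measures to the full analysis plan, which is not shown, so their absence is no fault.

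That unseen plan might also adjust for site. The article, however, names the primary test outright, and an adjusted primary test would then disagree with it.

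**Conclusion.** The point holds as a matter of efficiency only. The primary test does not use the strata in which women were randomized, so it is mildly conservative whenever live birth rates differ between sites. The cost is nil if all sites share one rate. It stays under 1 percentage point of power up to a between-site SD of 10 points, and under 2 at 15 points.

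These sizes rest on the assumed SDs, a two-sided 0.01 level, the planned 50% and 60% rates, and near-balance of the arms within sites. Validity and the planned power are not in question. The severity is low. The change is worth making because it costs almost nothing and conflicts with nothing else in the article.

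**What to change.** In the Data analysis plan, make the primary test of singleton live birth a Cochran-Mantel-Haenszel test stratified by study site, stated as being without continuity correction. Pair it with the matching Mantel-Haenszel risk difference. Fix in advance a rule for pooling very small sites. Keep the Pearson chi-square as a supportive analysis. Rare secondary and safety outcomes can stay with the chi-square or Fisher tests already named, since stratifying them by site would leave most strata sparse.

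The cost is a sentence or two of text. Site is already known from randomization, so no extra data or women are needed, and 735 (817 with dropout) per group can stand. Enrollment was still under way when the article was written, and assignments are known to investigators. The change should therefore be dated and documented before outcomes are compared by arm, so that it cannot look data-driven.
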